# ULB-Hopital Erasme*, and Department of Statistics, ULB-School of Public Health**, Bruxelles

# and AZ StJan***, Brugge

## Sponsors:

## Federal Public Service Public Health, Food Safety and Environment, Belgium.

## Cepheid, Europe.

## Introduction

Methicillin-resistant *Staphylococcus aureus* (MRSA) strains have become endemic pathogens in acute and chronic healthcare facilities in Belgium and are also spreading in the community. MRSA infection is causing increased public concern as it carries a significant risk of morbidity, mortality and has been linked to substantial excess healthcare costs (1). The increased risk of prolonged hospital stay and fatal outcome from bloodstream or surgical infection with MRSA, as compared with no infection or infection with methicillin-susceptible *S.aureus*, has been well documented (1).

Efficient control of MRSA transmission within healthcare facilities critically depends on screening for and isolation of MRSA carriers among admitted patients. Active surveillance cultures for MRSA are now part of clinical practice recommendations both in Europe and the USA (2-3). Indeed, studies have indicated that up to 70 % of the patient reservoir for MRSA among hospitalized patients can only be detected by active sampling and selective cultures of muco-cutaneous colonization sites, including the nares, throat, skin, wounds, rectum and insertion sites for invasive devices. MRSA colonization places the individual patient at increased risk of healthcare associated infection and constitutes a reservoir for transmission to other hospitalized patients. There is an urgent public health need for early and reliable detection of carriers of MRSA among patients admitted to healthcare facilities, to inform patient isolation and decontamination procedures, and thereby more effectively control cross-infection (4).

Detection of MRSA in muco-cutaneous swab specimens is typically performed by using selective and differential agar media, sometimes enhanced by enrichment broth culture which is incubated overnight before plating on selective agar (5). Traditional media contain an indicator system to presumptively identify *S.aureus*, such as mannitol and pH indicator like phenol red combined with inhibitory agents such as high NaCl concentration or antimicrobial agents. These media usually require 48 to 72 h before presumptive identification can be made, followed by confirmation on isolated colonies by additional testing which require up to 24 h (5). New selective agar media supplemented with cefoxitin and chromogenic enzyme substrates have shown improved performance, with some media allowing MRSA identification with > 80 % sensitivity and 99 % specificity after 18-24 h and with 95-100 % sensitivity and > 90 % specificity after 42-48 h (5).


Because of the increased cost of implementing routine high volume testing with these molecular assays, demonstration must be made of their added medical value and cost effectiveness for facilities fighting healthcare-associated MRSA infection. Likewise, the many studies that document the impact of rapid MRSA carrier screening on outbreak management and control of MRSA transmission within hospitals are subject to some degree of bias, such as uncontrolled/unplanned before-after design. Evidence from such intervention studies and from mathematical modeling suggests that enhanced rapidity and accuracy of molecular MRSA screening embedded in the “search-and destroy” policy should be highly cost-beneficial at hospital level in both endemic and low prevalence settings (10).

Five intervention studies using historical controls and assessing multiple interventions suggested effectiveness of rapid MRSA screening in surgical, intensive care or general acute care hospital settings (11-15). However, two recently published, large, well designed randomised controlled trials failed to confirm such a benefit in general wards or in planned surgery patients (16, 17).

Additional well-designed intervention trials are needed to clarify the medical and financial added-value of these strategies in diverse healthcare systems with different levels of MRSA endemicity and infection control policies. These require multidisciplinary technology assessment and system-wide practice change to be met. The present proposal attempts to contribute to this evaluation of medical benefit of PCR-based detection of MRSA carriers on reducing the risk of in-hospital transmission of MRSA in the Belgian healthcare setting.

## Study objectives

The general objectives of this intervention study to be conducted in parallel in two large Belgian hospitals are to measure the benefit of rapid (< 3 h) PCR detection of MRSA carriage upon admission on shortening the delay to implement contact isolation precautions for carriers and reducing of nosocomial MRSA transmission.

**Primary aim:**

Primary outcome: To determine if a ≥ 50 % reduction of incidence of nosocomial MRSA acquisition can be observed after replacing culture by PCR for universal MRSA screening of patients upon admission to high incidence units in two acute care hospitals

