**Secondary aims:**

To compare the following secondary outcomes during periods of MRSA carrier screening among hospital admissions by means of rapid PCR testing versus conventional culture:

1. Median time required for detection of MRSA carriage after admission
2. Median time required for starting isolation of MRSA carriers
3. Number of patient-days of MRSA carrier stay in non-isolated conditions
4. MRSA nosocomial infection rate
5. MRSA cross-transmission rate
6. Sensitivity and specificity of PCR vs conventional MRSA screening

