**Intervention study design**

The study will be a **cluster randomized intervention trial,** with **cross-over design** carried out in three phases:

(1) a 3 month screening reinforcement phase during which the adherence to the admission and discharge MRSA screening protocols will be promoted and monitored monthly to achieve > 80 % compliance rate, application of isolation precautions to MRSA colonized patients will be measured and checked to achieve > 80 % compliance and the MRSA acquisition rate will be checked to lie within 95 % confidence limits of the projected 3% estimate. In addition, the length of stay per ward will be measured and checked for homogeneous distributions.

(2) a 5 month conventional detection test (standard care) phase during which MRSA screening will be performed by optimized conventional culture methods 6 days a week during working hours.

(3) a 5 month rapid detection test intervention phase during which admission MRSA screening will be performed by rapid PCR testing 7 days a week during working hours.

After eligible wards in each hospital have been checked to meet these inclusion criteria in phase (1), the sequential order of inclusion of eligible study wards in phase (2) and (3) will be randomly assigned within each centre by assigning a number to each ward and using a computer generated list of random numbers per study arm in each hospital so that one half of the wards will start phase (2) for the first 5 months and then phase (3) for the following 5 months whereas the other study wards will be “crossed-over” to follow the reverse sequence. No wash-out period will be used between phase (2) and (3). If the analysis of patient length of stay by ward indicates homogeneous distribution with markedly different median values between wards, stratified randomisation of wards within short/long (below/above pooled median) stay groups will be considered.

The planned study start date is: November 3rd, 2008 for the baseline observation and completion is planned on December 31st, 2009 (post-poned to end January, 2010 see addendum).

Admission screening: evaluation of patient sampling procedures:

During the entire study period (baseline and intervention phase), the infection control nurse responsible for the study will perform daily rounds in each of the study wards to ensure that screening of all newly admitted patients is being done systematically and without delay.

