In addition, during a defined period, he or she will collect individual patient data on a subset of 20 % of included patients to identify risk factors for MRSA carriage based on history taking (notion of previously recorded MRSA carriage, transfer from other department or hospital, transfer from a nursing home, hospital stay in the previous year, attending outpatient care at a clinic in the previous year, presence of chronic skin sores, or living/working in a livestock farm, working as veterinarian or in a slaughterhouse). These data will be analysed to estimate the predictive value of these risk factors for the carriage of MRSA.

In the control arm, as per routine infection control policy in each institution, all patients admitted to study wards and presenting with will be sampled within 24 h after admission by taking swabs of anterior nares, throat, perineum and of any wounds, bladder catheter or intravenous catheter exit site (see appendix 1 for conventional MRSA screening procedures). Patients with previously recorded active MRSA carriage will be presumptively placed in contact isolation until three new series of conventional selective cultures of relevant body sites are found negative.

In the rapid test intervention arm, all patients admitted to study wards will be sampled within 24 h after admission. To ensure comparison of like with like, sample taking will include: (1) a swab from the anterior nares for PCR testing according to the test manufacturer’s instructions (see appendix 2 for rapid PCR screening test procedure); (2) the swab of anterior nares, and swabs from throat, perineum and of any wounds, bladder catheter or intravenous catheter exit site will be processed by conventional testing (see appendix 1 for conventional MRSA screening procedures). Patients with previously recorded active MRSA carriage will not be sampled for PCR testing but placed in pre-emptive isolation until three series of conventional selective cultures of relevant body sites are found negative.

Thus, patients in each arm will be managed identically, except that the rapid PCR test will be performed and its results made immediately available to infection control and clinical staff in the intervention arm.

MRSA isolates will be tested for mupirocin susceptibility and stored at -80°C for genotyping.

Additional contact isolation precautions.

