MRSA contact isolation precautions will be applied to hospitalised patients as per local policy (see appendix 3 for isolation procedures in HE and AZSJ hospitals) either when previously recorded in the laboratory information file as active MRSA carrier or as soon as newly detected by either culture or PCR. Patients will be released from isolation after three consecutive culture screens for MRSA are negative after the end of therapy. Topical decolonisation therapy will be applied as per routine protocol in each institution (see appendix 4 for decolonisation procedures in HE and AZSJ hospitals) to all patients with either a positive MRSA culture and/or PCR.

Notification of screening results and process time recording.

Results of MRSA screening tests will be notified electronically to clinicians by either the technologist or biologist on duty through the laboratory information system (LIS) as well as with a telephone call to the Infection Control study nurse (during working hours) or the unit head nurse (outwith working hours). For culture tests, both presumptive positive results based on colony pigmentation typical for MRSA on chromogenic selective culture medium as well confirmed identification results will be notified immediately by the same communication modes. The precise timing (date, hour, min) of all telephonic result notifications will be recorded in the LIS.

The date and time (hour; min) of patient admission to study ward, as well as of patient placement in contact isolation or release from isolation will be recorded by the infection control study nurse. The date and time (hour; min) of screening sample reception in the laboratory, as well as of result electronic notification will be recorded by the LIS.

Primary outcome monitoring and case finding procedures.

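### The primary aim asks about replacing culture by PCR, but the intervention arm keeps and acts on full culture, so the trial estimates only the effect of adding nasal PCR to culture

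*Protocol*

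**What the plan says.** Three places in the protocol present the comparison as PCR against culture:

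- Primary aim: the question is whether the reduction "can be observed after replacing culture by PCR for universal MRSA screening of patients upon admission".
- Secondary aims: outcomes are contrasted between screening periods "by means of rapid PCR testing versus conventional culture".
- Intervention study design, phase (3): "admission MRSA screening will be performed by rapid PCR testing 7 days a week during working hours". Continued culture is not mentioned there.

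The operational text, further on under Intervention study design, defines a different contrast:

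- Intervention-arm patients have "a swab from the anterior nares for PCR testing according to the test manufacturer", so PCR uses the nose only.
- The same patients also have nasal culture, and "swabs from throat, perineum and of any wounds, bladder catheter or intravenous catheter exit site will be processed by conventional testing". These are the control-arm sites.
- Patients with previously recorded active carriage "will not be sampled for PCR testing but placed in pre-emptive isolation"; their release depends on culture.
- Contact isolation starts for new carriers "as soon as newly detected by either culture or PCR". Decolonisation likewise follows a positive result from either test. Culture results are notified at once, with no restriction by arm.
- The protocol's own summary is: "Thus, patients in each arm will be managed identically, except that the rapid PCR test will be performed and its results made immediately available".

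**The concern.** The aim names a comparison that no arm makes. A carrier missed by nasal PCR, because carriage is only in the throat, perineum or a wound or because the strain escapes the assay, can still be found by culture and isolated in the intervention arm. If PCR truly replaced culture, that second route would be gone. The primary rate ratio is therefore an answer to one question printed under another.

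What is at stake is the claim that the result can carry. Paying for PCR on top of culture and substituting PCR for culture are different decisions, and the Introduction gives added value and cost-effectiveness as the reason for the study. If the aim stands as written, a favourable rate ratio formally answers a replacement question that was not tested.

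**Working it through.** **Step 1: which contrast is delivered.** Control arm: multi-site culture, acted on. Intervention arm: the same culture, acted on, plus nasal PCR, acted on. Culture is common to both arms, so the difference between them is the PCR result and its speed. Nothing in the protocol withholds or masks culture results in the intervention arm.

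**Step 2: do the protocol's counts agree with this reading?** They do.
- Sample size estimate: 1,850 per arm in each hospital, so 2 × 1,850 = 3,700 intervention patients and 2 × 3,700 = 7,400 in all.
- Secondary analysis E expects 3,700 matched nasal swabs tested in parallel, which is the whole intervention arm.
- The budget lists 7,400 admission cultures, which is both arms in full.
- The primary endpoint's at-risk population requires a negative admission culture in either arm, plus a negative PCR where one was done.

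**Step 3: when do the two questions have the same answer?** Take two assumptions from Study type and patient population: isolation cuts transmission 6-fold, and the intervention cuts unisolated stay from 3 days to 0. Set daily transmission at 6 when unisolated and 1 when isolated. Four further assumptions are mine and are not in the documents: a carrier stay of *L* days; a share *s* of culture-detectable carriers who are found by nasal PCR; culture finds the remaining carriers after 3 days; and carriers missed under replacement are never isolated.

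- Control: 3 × 6 + (*L* − 3) × 1 = *L* + 15
- Add-on: *s* × *L* + (1 − *s*) × (*L* + 15)
- Replacement: *s* × *L* + (1 − *s*) × 6*L*
- Replacement minus add-on, relative to control: (1 − *s*) × (5*L* − 15) / (*L* + 15)

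For any stay longer than 3 days the gap is zero only at *s* = 1, and otherwise the add-on looks better than replacement. With *L* = 10 the control value is 25, and transmission relative to control is:

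- *s* = 1: 10/25 = 0.40 for both.
- *s* = 0.985: 10.225/25 = 0.41 for add-on; 10.75/25 = 0.43 for replacement.
- *s* = 0.80: 13/25 = 0.52; 20/25 = 0.80.
- *s* = 0.60: 16/25 = 0.64; 30/25 = 1.20.

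At *s* = 0.80, the pair is 0.455 and 0.636 for a 7-day stay, and 0.657 and 1.143 for a 20-day stay.

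**Step 4: can the documents fix *s*?** No. The Introduction gives a preliminary Xpert sensitivity of 98.5%, without naming the specimen or the comparator. It lists throat, skin, wounds and rectum among colonisation sites but gives no share of carriers positive only outside the nose. The 98.5% row applies only if that share is zero and the preliminary figure holds. The lower rows show how the answer depends on *s*; they are not estimates for this trial.

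**The case against.** The best defence is that the protocol states the add-on contrast openly. The arms are declared identical apart from PCR. The general objective is about shortening the delay to isolation. The 50% effect is derived from earlier isolation, not from removing culture. The ethics section relies on the same standard care for everyone. Retained culture is also needed: it defines the at-risk denominator, is the reference for PCR accuracy, and supplies isolates for mupirocin testing and typing. The secondary-aims wording can be read as a label for the two periods, and its sixth item, PCR accuracy, presupposes parallel culture. On this view the fault is loose wording, and no arm, model or sample size changes.

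Most of this stands, and it shows that the design is sound. It does not rescue the primary aim, which is where the trial says what its main result means.

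A reader might infer more than the text supports:

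- *That the investigators plan to recommend dropping culture.* No such conclusion is planned anywhere. The rate ratio is a fair estimate of the contrast the procedures define, and is favourable only relative to a policy the trial does not run.
- *That culture catches every carrier PCR misses.* The Introduction puts chromogenic culture at above 80% sensitivity at 18–24 h and 95–100% at 42–48 h, and the screening compliance target is above 80%. Culture also acts only after its usual delay.
- *That a definite share of carriers would be missed under replacement.* Any such figure rests on an assumed extra-nasal share. The sensitivity above 93% in the Introduction is a bound for another manufacturer's assay.
- *That replacement must mean nose-only PCR.* Trial sampling for PCR is nasal, but the Dutch-language Xpert procedure describes nose-throat-perineum swabs. Culture is retained on either reading.

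**Conclusion.** The point holds as a contradiction between the stated primary question and the design. The rate ratio estimates culture plus rapid nasal PCR versus culture alone and cannot show the effect of replacing culture. This follows from the arm definitions and needs no numerical assumption.

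The size of the difference between the two questions is unknown. In the illustration it runs from negligible, if nasal PCR finds nearly every carrier that culture finds, to a reversal of the conclusion, if it misses a large share. The documents do not say where this trial lies. No figure, endpoint or model in the protocol is wrong on this account, and retaining culture is justified. What must change is the question that the result is said to answer.

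**What to change.** 1. Reword the primary aim as the effect of *adding rapid nasal PCR to conventional multi-site culture screening, versus culture alone*. Align the secondary aims and the description of phase (3), saying there that culture continues.
2. State in the analysis section that the rate ratio supports no inference about replacing culture.
3. Extend the accuracy analysis. Secondary endpoint 5 and secondary analysis E already yield the count of carriers positive on nasal culture but PCR-negative. Add a table of intervention-arm admission carriers found by culture at any site but negative on nasal PCR, with their time to isolation. Show patients without a valid PCR result separately, including previously recorded carriers, who are not PCR-tested. Cultures are taken with a separate swab per site and isolation times are already recorded, so no new data are needed. The table counts the carriers nasal PCR alone would have missed; it does not estimate the transmission that would follow.

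The cost is a few sentences of protocol text, one extra table and a narrower claim. Arms, sampling, sample size and primary model stay as they are.

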**Secondary aims:**

To compare the following secondary outcomes during periods of MRSA carrier screening among hospital admissions by means of rapid PCR testing versus conventional culture:

1. Median time required for detection of MRSA carriage after admission
2. Median time required for starting isolation of MRSA carriers
3. Number of patient-days of MRSA carrier stay in non-isolated conditions
4. MRSA nosocomial infection rate
5. MRSA cross-transmission rate
6. Sensitivity and specificity of PCR vs conventional MRSA screening

## Study design

**Study type and patient population**

The study will be an open label, **cluster randomized intervention trial,** with **cross-over design.** It will be carried out in parallel over a one year period in two large hospitals in

1. patients admitted to high risk surgical, medical and geriatric wards of Erasme hospital (7 to 8 wards)
2. patients admitted to the intensive care departments, medical and geriatric wards of AZ St Jan hospital (6 to 7 ward).

The Erasme hospital is an 858-beds academic hospital located in Brussels, including medical and surgical care departments. The AZ-St Jan hospital is an 800-bed general teaching hospital located in Brugge, including medical and surgical care departments. Both institutions have an integrated MRSA surveillance and control program in place for over 10 years. These programs adhere to the national recommendations for MRSA control in acute care hospitals (BICS-CSH/HGR 2003). These include: active screening of MRSA carriers on admission by selective culture of nasal, throat and wound sites in high risk patients and/or units, flagging of previously detected MRSA carrier patients at re-admission, placement of MRSA carriers in single room with contact isolation precautions and decolonisation therapy of carriers with nasal mupirocin and antiseptic bathing for 5 days.

The choice of a minimum size of effect of 50% reduction in MRSA acquisition is based on the assumption that a 6-fold reduction of transmission rate can be expected from placing MRSA positive patients in isolation, and that the reduction from 3 to 0 days of unisolated stay can be expected by the intervention. Assuming a baseline rate of 3% nosocomial acquisition rate in the exposed population of study wards, the study population will include 3,700 patients in each hospital with approximately 50 new cases of MRSA acquisition in the control arm (n= 1,850 patients) versus 25 new cases in the intervention arm (n= 1,850 patients).

Selection of study wards in each hospital will be defined based on determination f wards with highest MRSA nosocomial incidence documented by local surveillance data for the pre-trial period first half of 2007, to meet the expected number of new cases per 5-month period above. Because discharge surveillance is not currently performed in the study centres, it is assumed that adding pre-discharge screening of MRSA carriers will increase the detection rate two-fold and double the actual (3%) versus retrospectively observed incidence (1.5 %). This assumption will be checked during the 3-month baseline screening reinforcement phase. Any type of adult care ward will be considered for inclusion in the study, including intensive care, medical, surgical and geriatric wards.

